**5.4 LPS administration**

A physician shall prepare the LPS solution, load the Pfeiffer Bidose device and complete a record form. The procedure will be checked and signed by a senior member of ICRRU staff.

LPS solutions (Ultrapure LPS E-Coli 0111:B4 (*Invivogen*) and placebo will be administered from a Pfeiffer Bidose nasal delivery device by a physician.

This is a high quality non-GMP source of LPS.

LPS solution (250l) will be prepared at 10, 100, 300 and 1000g/ml,

100l is administered to each nostril, both nostrils will be sprayed

The dose per nostril corresponds to 1, 10, 30 and 100g

Weights will be recorded before and after each actuation from the Pfeiffer Bidose.

## Regimen Assignment

Subjects will be assigned to a sequence in accordance with the randomisation schedule generated prior to the start of the study. The randomisation will be balanced over the 5 nasal challenge sequences and will be generated using RandAll, the GSK web-server based clinical trials randomisation validated system.

A description of each challenge sequence is provided in Table 1. The LPS dose corresponds to the dose administered to each nostril.

Table 1. Nasal LPS Dosage Regimen Sequence

| Sequence | Number of subjects receiving sequence | Nasal Challenge 1 | Nasal Challenge 2 | Nasal Challenge 3 | Nasal Challenge 4 | Nasal Challenge 5 |
| --- | --- | --- | --- | --- | --- | --- |
| 1 | 3 | placebo | 1μg LPS | 10μg LPS | 30μg LPS | 100μg LPS |
| 2 | 3 | 1μg LPS | 30μg LPS | placebo | 100μg LPS | 10μg LPS |
| 3 | 3 | 10μg LPS | 100μg LPS | 30μg LPS | 1μg LPS | placebo |
| 4 | 3 | 30μg LPS | 10μg LPS | 100μg LPS | placebo | 1μg LPS |
| 5 | 3 | 100μg LPS | Placebo | 1μg LPS | 10μg LPS | 30μg LPS |

A washout time of 12-28 days will be employed between challenges

1. **Samples and Measures**

**7.1 Samples**

- Nasosorption (right nostril) will be performed before and then 30min, 1h, 2h and hourly to 10h, 24h
- Nasal lavage (left nostril) will be performed at times before (-30 min, 2, 4, 8, 24h.
- Nasal scrape (left nostril) will be carried out after lavage on 4 occasions

……………before (-30 min), 3h, 6h, 24h.

The scrapes will be performed progressively more deeply into the posterior aspect of the nostril, from the inferior aspect of the inferior turbinate

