**2.2 Primary Objective**

The principal research questions (primary end point, PEP):

- Can we develop a well tolerated, robust and reproducible (validated) nasal LPS challenge system in terms of ICAM-1 induction ?
- Can we document a dose response and time course to nasal LPS in terms of cell influx, cytokine and chemokine release, and nasal epithelial curettage (Rhinoprobe) mRNA expression ?
- To assess the unstimulated expression of ICAM-1 in nasal epithelial scrapes.
- To provide a nasal challenge method with LPS to enable a “proof of target pharmacology” for a therapy directed against ICAM-1 induction. This may also permit dosage optimisation in relation to clinical efficacy studies.

1. **Study Design**

5-way crossover study, randomized, single-blind, placebo-controlled, dose-response to LPS.

A single cohort of 15 healthy volunteers will be studied in a 5-way cross-over study (4 doses of LPS versus placebo), for a minimum of 12 to complete.

A balanced Latin square randomized design will be used.

Total study duration: 6-9 months

1. **Study population**

For this clinical study it is proposed to study healthy volunteers with no history of allergy, nor any other significant illnesses or therapy.

15 healthy volunteers will be recruited, for a minimum of 12 to complete

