**7.2 Measures**

- Modified TNSS: pain/itching/discomfort, obstruction, sneezing, nasal discharge
- Systemic adverse effects:

fever (record temperature at pre, 2h, 4h, 8h)

flu-like illness (grade severity, 1-3)

myalgia (grade severity, 1-3)

- Nasal sniff pressures, PNIF
- Nasosorption: MSD multiplex (MIP-1α, IL-1β, IL-6, IL-8, TNF-α. TGF-, IFN-α) from MSD, with analysis at GSK
- Nasosorption for s-ICAM-1 by ELISA, with analysis at GSK
- Nasal lavage cell count and cytospin for cell differential (neutrophils, macrophages, eosinophils, epithelial cells), with assessment at ICRRU
- Nasal scrapes (Rhinoprobe) for gene expression with analysis at GSK

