### 8.3.2 Statistical Analyses

Each of the measures will be summarised descriptively by dose and time using appropriate summary statistics. If appropriate, response variables will be transformed (e.g. log-transformed). Gene expression data will be normalised by house-keeper gene. The TNSS will be calculated by summing the scores of nasal blockage, nasal discharge/rhinorrhoea, nasal burning/itching/pain sensation, and sneezing at each timepoint. Weighted means of symptom scores will be calculated over the time interval 0 to 10h.

TNSS, nasal sniff pressures, nasosorption measures and gene expression data from the nasal scrapes will each be plotted against time, with a separate plot for each subject and measure, and with LPS dose and placebo represented by separate lines on the plots. Summary statistics (e.g. mean +/- 95% confidence intervals or median and interquartile range) for nasal lavage and gene expression data will be plotted by dose against time.

Correlations will be explored using scatter plots for the following measures:

- Weighted means TNSS vs. maximum TNF-α
- Weighted means TNSS vs. maximum IL-8
- Weighted means TNSS vs. maximum s-ICAM-1
- Maximum ICAM-1 expression vs. maximum TNF-α

Reproducibility of the nasal LPS challenge for ICAM-1 expression and TNF-α will be explored using the following subsets of data:

- Predose data for each period to explore intra-subject variability.
  Parameter vs. period number will be plotted with a separate line for each subject to explore whether there is a period effect. Box and whisker plots will also be used to summarise the parameter by period.
- Placebo period data – Parameter vs time will be plotted with a separate line for each subject to explore whether there is a time-course effect. Box and whisker plots will also be used to summarise the parameter over time.

Box and whisker plots for ICAM-1 expression and TNF-α and dose and time will be presented to investigate whether these measures return to baseline after 24h.

Additional exploratory analyses may be performed to further characterize the expression profile of ICAM following nasal LPS challenge.

1. **Study Schedule**

|  | Screening | Sessions 1-5 | | | | | | | | | | | | | | Tel F/up |
| --- | --- | --- | --- | --- | --- | --- | --- | --- | --- | --- | --- | --- | --- | --- | --- | --- |
|  |  | -30m to  -15m | 0 | 30m | 1h | 2h | 3h | 4h | 5h | 6h | 7h | 8h | 9h | 10h | 24h |  |

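### Scrape depth increases with scrape time within each session, so the uncorrected mRNA time course, maximum and 24h recovery in 8.3.2 cannot be separated from anatomical site

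*Protocol*

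**What the plan says.** Protocol 7.1 states "Nasal scrape (left nostril) will be carried out after lavage on 4 occasions", at the times "before (-30 min), 3h, 6h, 24h". On position it adds: "The scrapes will be performed progressively more deeply into the posterior aspect of the nostril", starting at the underside of the inferior turbinate. It mentions no rotation of positions and no recording of them, and does not say outright that each session starts again at the same depth.

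The scrapes supply the mRNA data (7.2: "Nasal scrapes (Rhinoprobe) for gene expression with analysis at GSK"). ICAM-1 is also measured as a soluble protein from the right nostril (7.2: "Nasosorption for s-ICAM-1 by ELISA, with analysis at GSK").

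The time course is an objective. Section 2.2 asks "Can we document a dose response and time course to nasal LPS", and lists curettage mRNA among the read-outs. Section 8.3.2 plans:

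- gene expression against time, per subject and summarised by dose;
- a scatter plot of each subject's highest ICAM-1 expression against the highest TNF-α;
- placebo-period plots of ICAM-1 expression over time;
- box plots of ICAM-1 expression and TNF-α by dose and time, which "will be presented to investigate whether these measures return to baseline after 24h".

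No comparison with placebo is named for the maximum or for the return to baseline.

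**The concern.** Each later scrape comes from a more posterior site than the one before. If cell mix or resting ICAM-1 expression changes from front to back, that gradient will look like a response over time. A rise at 24h could be a slow LPS effect or simply a deeper site. A fall could be recovery, or a site with lower expression. The maximum over the post-dose scrapes has the same ambiguity, because the time of the peak is also the depth of the peak.

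The study is exploratory (8.1), but section 2 gives its purpose as a challenge model for later anti-ICAM-1 therapies. A misread peak time or recovery time would carry forward into the sampling times and washout of those studies.

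**Working it through.** The protocol gives no figure to reproduce: no effect size, SD or site gradient. The check is therefore of what the design can estimate, followed by an illustration over an assumed range.

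**Inputs.** Table 1: 5 sequences × 3 subjects = 15 subjects, 5 periods each. Section 7.1: 4 scrapes per session at increasing depth. Total 15 × 5 × 4 = 300 scrapes. Assumption: the depth sequence is the same in every session.

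**Model.** For one subject, let y(d,t) be log2 expression under dose d at time t, with site k(t) fixed by the order of scraping:

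y(d,t) = subject + period + dose(d) + time(t) + site(k(t)) + [dose × time](d,t) + error

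**Rank of the design matrix (number of separately estimable terms).**

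| Terms | Rank as planned | Rank if position order is rotated over subjects and periods |
|---|---|---|
| subject + period + dose | 15 + 4 + 4 = 23 | 23 |
| + time | 23 + 3 = 26 | 26 |
| + site | 26 (adds 0) | 29 |
| + dose × time | 26 + 12 = 38 | 41 |
| + dose × site | 38 (adds 0) | 53 |

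Three things follow for the plan as written:

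1. Site adds nothing once time is in the model, so the two are fully aliased. Fewer completers (12 × 5 × 4 = 240 scrapes) would not change this.
2. All 12 LPS-versus-placebo contrasts in change over time remain estimable, provided the site effect is the same under LPS and placebo.
3. Dose × site adds nothing after dose × time. An LPS response that varies with depth, for example through uneven spray deposition, cannot be told from one that varies with time, even after placebo correction.

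**What each comparison contains** (site 1 at pre-dose, site 4 at 24h):

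- Raw 24h minus pre-dose = [time(24h) − time(pre)] + [site(4) − site(1)] + change due to LPS.
- LPS minus placebo at 24h: time(24h) and site(4) occur in both sessions and cancel.
- Placebo-corrected change from pre-dose: time and site terms cancel, and so do additive period and session terms.

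**Illustration.** With a shift of g log2 units per step, no true time effect and no LPS effect, the apparent ratio to baseline is 2^(g × steps):

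| g (assumed) | 3h (1 step) | 6h (2 steps) | 24h (3 steps) |
|---|---|---|---|
| 0.1 | 1.07 | 1.15 | 2^0.3 = 1.23 |
| 0.25 | 1.19 | 1.41 | 2^0.75 = 1.68 |
| 0.5 | 1.41 | 2.00 | 2^1.5 = 2.83 |

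The same shift contributes zero to the LPS-minus-placebo difference at each time.

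**Lavage timing.** Lavage is at −30 min, 2, 4, 8 and 24h; scrapes are at −30 min, 3, 6 and 24h. Two of the four scrapes share a nominal time with a lavage. The 3h scrape follows the 2h lavage by 3 − 2 = 1h, and the 6h scrape follows the 4h lavage by 6 − 4 = 2h.

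**The case against.** A reader might infer that the ICAM-1 results as a whole are hopelessly confounded with site. The documents do not support that. Every subject has a placebo session with the same four scrapes at the same times, and Table 1 balances doses over periods. Dose response at a fixed time, which 8.1 places in the primary objective, is not confounded with an additive site effect. Section 8.3.2 already shows placebo as its own line on each subject's plot, so the right comparison is visible by eye. Its placebo-period plot would reveal a drift, though not whether time, depth or repeated scraping caused it. Nasosorption s-ICAM-1, cytokines and lavage cells do not depend on scrape depth. All of this stands, and it limits the point to uncorrected scrape mRNA.

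A reader might also infer that the 3h and 6h scrapes cannot follow a lavage, so that 7.1 contradicts its own schedule. That does not hold: they follow the 2h and 4h lavages. What varies is the interval, and it is the same under every dose.

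It can further be said that a derived variable such as LPS minus placebo belongs in the SAP, which is not at hand and may already define it. That is fair as to detail. But the order of sampling is fixed in the protocol and no later analysis plan can undo it, while 8.3.2 itself frames recovery as a return to baseline.

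Finally, the gradient is assumed and the study tests no formal hypothesis. Both are true, so the size of any bias is unknown.

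**Conclusion.** The point holds for scrape mRNA. Within a session, depth and time are fully aliased, so the uncorrected time course, the maximum and the 24h-versus-baseline comparison cannot be attributed to time alone. Under an assumed linear gradient of 0.1 to 0.5 log2 units per step, the false 24h/baseline ratio is 1.23 to 2.83; the documents neither support nor exclude any value in that range.

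Same-time LPS-versus-placebo and dose comparisons escape an additive site effect. They do not escape an LPS effect that varies with depth.

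Two assumptions matter. First, the depth sequence is taken to restart at the same point each session. If it carried on across sessions, within-session aliasing would remain and depth would also follow period, so single-subject differences from placebo would no longer cancel the site term. Second, ICAM-1 expression in 8.3.2 is taken to include the scrape measure. The section lists s-ICAM-1 separately, which suggests this, but it does not say so.

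**What to change.** **In 8.3.2.** State which measure ICAM-1 expression refers to. For scrapes, base the peak and the 24h recovery on the within-subject LPS-minus-placebo difference at the same time point, or on the placebo-corrected change from pre-dose, in place of a raw comparison with pre-dose. Take the peak as the largest of those differences.

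**In 7.1.** State that each session's depth sequence starts at the same point, and record the position of each scrape. Clarify the wording on scraping after lavage: only the −30 min and 24h scrapes share a nominal time with a lavage, while those at 3h and 6h follow one by 1h and 2h.

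**Cost.** No extra scrapes; analysis wording and one recorded item per scrape. The downside is noise from the placebo session. With independent scrape variance σ² and session variance ω², a raw change from pre-dose has variance 2σ², the same-time difference 2σ² + 2ω², and the placebo-corrected change 4σ².

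**Optional, if operationally feasible.** Vary the order of positions over time across subjects so that time and site can be separated, including for a depth-dependent LPS effect. This changes the sampling procedure. Four position orders cannot be exactly balanced over 15 subjects (15/4 = 3.75). If each subject keeps one order throughout, time and depth also stay aliased in that subject's own plots. It is not a condition for the analysis change above.

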**7.2 Measures**

- Modified TNSS: pain/itching/discomfort, obstruction, sneezing, nasal discharge
- Systemic adverse effects:

fever (record temperature at pre, 2h, 4h, 8h)

flu-like illness (grade severity, 1-3)

myalgia (grade severity, 1-3)

- Nasal sniff pressures, PNIF
- Nasosorption: MSD multiplex (MIP-1α, IL-1β, IL-6, IL-8, TNF-α. TGF-, IFN-α) from MSD, with analysis at GSK
- Nasosorption for s-ICAM-1 by ELISA, with analysis at GSK
- Nasal lavage cell count and cytospin for cell differential (neutrophils, macrophages, eosinophils, epithelial cells), with assessment at ICRRU
- Nasal scrapes (Rhinoprobe) for gene expression with analysis at GSK

# Data Analysis and Statistical Considerations

## 8.1 Hypotheses

The primary objective for this study is to explore the effects of LPS challenge on ICAM-1 expression in healthy volunteers and determine a dose response relationship. This study is hypothesis generating rather than formal hypothesis testing.

## 8.2 Study Design Considerations

### 8.2.1 Sample Size Assumptions

The study will recruit 15 healthy volunteers in order to ensure 12 subjects complete the study. Any replacement subjects will be assigned to the same regimen sequence as the subject that they are replacing.

No statistical techniques will be used to calculate the sample size. The sample will be based primarily on feasibility.

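### Twelve completers cannot be spread evenly over five sequences, so by-dose summaries that ignore period carry a small session imbalance (minor)

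*Protocol*

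**What the plan says.** The Study Design text of the protocol states: "A balanced Latin square randomized design will be used". Under Regimen Assignment, "The randomisation will be balanced over the 5 nasal challenge sequences", and Table 1 gives 3 under "Number of subjects receiving sequence" for each of the five sequences, 15 in all.

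The completion target is lower. The Study population text says "15 healthy volunteers will be recruited, for a minimum of 12 to complete", and 8.2.1 says "The study will recruit 15 healthy volunteers in order to ensure 12 subjects complete the study". Neither place sets a condition on which sequences the 12 come from. The number has no statistical derivation: "No statistical techniques will be used to calculate the sample size".

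On losses, 8.2.1 adds: "Any replacement subjects will be assigned to the same regimen sequence as the subject that they are replacing". It does not say when a loss is replaced.

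On analysis, 8.3.2 says "Each of the measures will be summarised descriptively by dose and time using appropriate summary statistics". Period appears only in plots of pre-dose ICAM-1 expression and TNF-α by period number. Section 8.3.1 uses everyone with at least one challenge for all output.

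**The concern.** A Latin square is chosen so that each dose falls equally often in each session. A change over the five sessions that affects all doses alike then cancels from a simple comparison of dose means. Such a change could come from learning on the symptom score, repeated scraping of the same nostril, season or assay. The cancellation needs equal numbers per sequence. The protocol accepts a completer number at which this is impossible, and its stated summaries have no other protection against session effects. If drift exists, part of it enters the LPS-versus-placebo differences and the apparent dose ordering, and 8.1 makes the dose-response relationship part of the primary objective. The protocol treats a period effect as an open question, but looks for it only in pre-dose values of two measures. That look does not correct the post-challenge summaries.

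**Working it through.** **Inputs.** Table 1 (sequences and 3 subjects each), 12 completers (8.2.1), All Subjects population (8.3.1). The protocol gives no dropout rate and no drift size.

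**Step 1: the planned design.** Each dose occurs once in every session across the five sequences. With 3 per sequence, each dose's mean session is 3 × (1+2+3+4+5)/15 = 45/15 = 3.0. At 15 the design is balanced, as the protocol says.

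**Step 2: 12 completers.** Let n₁…n₅ be the completers per sequence. Because Table 1 is a Latin square, the number of times a dose appears in a given session equals the n of the one sequence that puts it there. Equal cells therefore need equal n, and 12/5 = 2.4 is not a whole number. Balance on mean session alone is also impossible. The 5 × 5 matrix of session positions is invertible (determinant 1200), so equal mean sessions would require every n to be 2.4.

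**Step 3: worked examples (completers only).** Placebo is in session 1, 3, 5, 4, 2 of sequences 1 to 5, 1 µg in 2, 1, 4, 5, 3, and 100 µg in 5, 4, 2, 3, 1.

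- One loss in each of sequences 1, 4 and 5 leaves 2, 3, 3, 2, 2.
  - Placebo: (2×1 + 3×3 + 3×5 + 2×4 + 2×2)/12 = 38/12 = 3.17.
  - 1 µg: (2×2 + 3×1 + 3×4 + 2×5 + 2×3)/12 = 35/12 = 2.92. The gap is 3/12 = 0.25 session.
- All three losses in sequence 1 leave 0, 3, 3, 3, 3.
  - Placebo: 3 × (3+5+4+2)/12 = 42/12 = 3.5.
  - 100 µg: 3 × (4+2+3+1)/12 = 30/12 = 2.5. The gap is 1.0 session.

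**Step 4: all 455 ways of losing 3 of 15, completers only.** Largest dose-versus-placebo gap in mean session:

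| Completers per sequence | Patterns | Share | Average gap | Maximum |
| --- | --- | --- | --- | --- |
| 3,3,2,2,2 | 270 | 59% | 0.33 | 0.50 |
| 3,3,3,2,1 | 180 | 40% | 0.52 | 0.83 |
| 3,3,3,3,0 | 5 | 1% | 0.80 | 1.0 |
| All | 455 | 100% | 0.41 | 1.0 |

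The minimum over all patterns is 0.17, so none is balanced.

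**Step 5: the planned population.** Each of the three dropouts keeps 1 to 4 sessions of data: 455 × 4³ = 29,120 patterns. None is balanced. The largest dose-versus-placebo gap averages 0.23 (range 0.07 to 0.75) and exceeds 0.5 in 0.4% of patterns.

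**Step 6: from gap to bias.** For a linear drift of d per session, a contrast shifts by d × gap. Purely as an illustration, assume d is 5 to 20% of the response. The average All Subjects gap then gives 0.23 × 5% = 1.2% up to 0.23 × 20% = 4.6%. The extreme of 0.75 gives 3.75% to 15%.

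**Step 7: cost of a period term at 12 completers.** With fixed subject effects, all dose contrasts remain estimable. Their variance rises by at most 1.4% (3,3,2,2,2), 3.7% (3,3,3,2,1) or 6.7% (3,3,3,3,0).

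**The case against.** Five arguments stand against giving this much weight.

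1. **The 1.0-session gap.** It is tempting to quote it as the size of the problem. It needs a whole sequence to be lost (5 of 455 patterns) and the leavers' data to be discarded. Section 8.3.1 keeps those data, which lowers the average from 0.41 to 0.23. This stands.
2. **No systematic direction.** The gap reported is the largest of four contrasts. Over all loss patterns the signed gap averages zero for every dose, so random dropout gives chance imbalance. This stands, although one trial realises one pattern.
3. **Twelve is a floor.** If every loss were replaced in its own sequence by someone who completes, the study would return to 3 per sequence. A reader might infer that the replacement rule contradicts the over-recruitment. It does not: it fixes the sequence of any replacement and is compatible with replacing nobody. But because no trigger is stated, the rule does not guarantee balance either.
4. **The analysis plan.** A period-adjusted model may be in a SAP that is not shown, and 8.3.2 leaves room for further exploratory analyses. The absence of a model from the protocol is therefore not an error in itself. What remains is that the summaries 8.3.2 does fix take no account of period.
5. **The study's status.** Section 8.1 calls it hypothesis generating. No test or threshold turns on a fraction of a session.

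**Conclusion.** The point holds, and it is minor. With three unreplaced losses, dose and session are never exactly balanced. The typical imbalance is about a quarter of a session in the planned population and about 0.4 among completers. It biases the by-dose summaries only if responses drift over sessions, and the protocol gives no information on the size of any drift. The averages assume that all loss patterns are equally likely and, for All Subjects, that each dropout is equally likely to have had 1, 2, 3 or 4 sessions. That balance is never exact does not depend on these assumptions.

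A reader might infer that the dose response will be materially biased or that the design fails at 12. The documents do not support that: every completer receives all five challenges, the confounding is partial, and all dose contrasts can still be estimated with period in the model.

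**What to change.** In 8.3.2, add that for the main response measures, dose-versus-placebo estimates with confidence intervals will be reported beside the raw by-dose summaries. They should come from a model with subject, period (as a category) and dose, on the log scale where appropriate. This removes any session effect that is additive on the analysis scale. It does not remove carry-over or a session effect that differs by dose. If the SAP already contains such a model, a reference to it is enough.

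The cost is a little more analysis and a variance increase of about 1 to 7% at 12 completers. No change to recruitment is needed.

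Two additions to 8.2.1 are optional. One is to state when a loss will be replaced. The other is to ask for at least 2 completers in each sequence. The second limits the completers-only gap to 0.5 session (average 0.33) but leaves 12 unbalanced and may require extra enrolment, so it does not replace the period term.
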